##### STS-10

The 10 times sitting-stereotaxic position test (STS-10) is a common method for evaluating muscle strength and endurance of the lower limbs, which is easy to use, safe, and has high specificity [43]. Specific operation method where the patients were asked to cross their hands in front of their chest while sitting in the same standard-height chair so that they could withstand the speed of repeatedly standing up and sitting down 10 times. A stopwatch was used to note the time, and the 10th hip contact with the chair surface was considered the end of the exercise. A shorter time indicated better lower limb muscle strength.

##### SDS

The SDS, which was developed by Liu et al [44] in 1965, was primarily for patients’ rating of the severity of their self-depression. It is widely used in clinical studies to observe changes in patients’ depressive mood in response to interventions. The scale consists of 20 entries reflecting subjective feelings of depression, including 4 dimensions: psychotic affective symptoms, somatic disorders, psychomotor disorders, and depressive mental disorders. Each entry was scored on a 4-point scale according to the frequency of symptoms, and except for 10 entries that were scored on a 4‐1 reverse scale, the other 10 entries were scored on a 1‐4 positive scale. The total crude score was obtained by summing the entries, and the normal upper limit of the total crude score was 80, with a lower score indicating a better status. The standardized score was the integer obtained by multiplying the total crude score by 1.25. According to the Chinese normative results, the cutoff value of the SDS standardized score is 53, with no depression below 53, mild depression between 53 and 62, moderate depression between 63 and 72, and severe depression above 72.

##### SF-36

The QoL of the study participants was assessed using the SF-36, a concise health survey questionnaire developed by the Boston Health Research Institute in the United States. The Chinese version of the SF-36, developed by [name] of Sun Yat-sen University of Medical Sciences was used in this study [45]. The scale contains 8 dimensions: vitality, physical functioning, bodily pain, general health perceptions, physical role functioning, emotional role functioning, social role functioning, and mental health, comprehensively summarizing the respondents’ QoL. The scale has 36 entries, each with a different scoring scale. Each dimension is scored as the ratio of the actual score for that dimension minus the difference between the lowest possible score for that dimension and the highest and lowest possible scores, with the ratio multiplied by a factor of 100 to give the final score for that dimension. The score for each dimension ranges from 0 to 100, and the scale total is the sum of the scores for each dimension, ranging from 0 to 800, with higher scores representing better QoL.

### Data Collection

Research team members must be trained in standardized measurement methods. Furthermore, baseline data must be collected before and after 8 weeks of treatment. The specific research program is detailed in Figure 1.

**Figure 1. F1:**
[figure not shown]
Study flowchart. FRAIL: Fatigue, Resistance, Ambulation, Illness, and Weight Loss; SDS: Self-Rating Depression Scale; SF-36: Short Form Health Survey Questionnaire; STS-10: 10 times sit-to-stand.

### Quality Control

A preliminary trial plan should be developed, followed by pilot tests. It is critical to follow the established inclusion and exclusion criteria to ensure that baseline conditions across groups are balanced. Furthermore, compliance with the intervention measures and data integrity must be evaluated regularly. It is essential to provide comprehensive information regarding the advantages of the intervention, offer assistance and encouragement, and use WeChat groups for supervision to improve patient compliance.

### Statistical Methods

#### Statistical Analysis

The database was established using Microsoft Excel software, and SPSS (version 25.0; IBM Corp) was used for statistical analysis and processing of all data. A bilateral test was used for statistical analysis; *α*=.05 was used as the test level, and *P*<.05 was considered statistically significant.

#### Descriptive Statistical Analysis

The measurement sample data that conform to a normal distribution are represented as mean (SD), and the measurement sample data that conform to a skewed distribution are represented as median (IQR). The frequency and composition ratio are used to describe the data of counting samples.

#### Statistical Inference

Baseline characteristics were comparable across groups. Continuous variables were analyzed using one-way ANOVA (normally distributed data) or rank-sum test; categorical data were assessed with chi-square tests. Within-group pre-post comparisons used paired 2-tailed *t* tests (normal data) or rank-sum tests. Between-group differences postintervention were evaluated using one-way ANOVA (with least significant difference post hoc testing if significant) or rank-sum tests, as appropriate. Categorical outcomes were compared using chi-square tests.

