**Methods:**

This is a randomized controlled study to be conducted in the Affiliated Hospital of Chengdu University of Traditional Chinese Medicine, comprising 114 patients to be treated using MHD. Patients who meet the inclusion and exclusion criteria will be randomly divided into 3 groups: the control group will receive only conventional hemodialysis and care, the acupoint massage group will receive acupoint massage treatment in addition to the control group treatment, and the sitting combined with acupoint massage group will receive sitting Baduanjin combined with acupoint massage and the control group treatment. We aim to comprehensively evaluate the clinical efficacy by comparing the FRAIL (Fatigue, Resistance, Ambulation, Illness, and Weight Loss) scale scores, grip strength, 10 times sit-to-stand test, Self-Rating Depression Scale scores, and QoL (Short Form Health Survey Questionnaire) scores before and after 8 weeks of treatment among the 3 groups. Statistical analysis will be conducted using the Statistical Package for the Social Sciences software (version 25.0; IBM Corporation).

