**Inclusion criteria**
Age: 45‐75 years with end-stage renal disease (uremia stage).Dialysis duration: receiving hemodialysis treatment ≥3 months, 3 times a week, and 4 hours per session, with stable vital signs.Frailty status: evaluated using the FRAIL (Fatigue, Resistance, Ambulation, Illness, and Weight Loss) scale, with scores of ≥1 indicating prefrailty or frailty.Cognitive and communication ability: clear consciousness, normal hearing, and ability to communicate normally.Physical function: no physical activity disorders, no regular exercise, able to understand and follow demonstration actions.Acupoint skin condition: intact skin at acupoint massage sites.Voluntary participation: willing to participate in the study.

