#### Primary Evaluation Indicator (FRAIL Scale Score)

To assess the severity of frailty in patients, the scores before and after the intervention were compared as follows.

Decline: the FRAIL scale, a simple frailty measurement tool developed by the International Society for Nutrition and Aging in 2008 and derived from the Fried Frailty Scale, which has been widely used in different populations, is quick and easy to use and predicts the occurrence of adverse outcomes. The scale consists of 5 entries: fatigue, increased resistance or decreased endurance, decreased free mobility, disease conditions, and decreased body mass. Each entry was assigned 1 point, and the total score ranged from 0 to 5, with 0 indicating no debility, 1‐2 indicating debilitating, and ≥3 indicating debilitating. A large foreign cohort study confirmed the good predictive validity of the FRAIL scale for impairment of daily activities and the occurrence of death [40]. Compared with other debilitation measurement tools, the FRAIL scale is most closely associated with dialysis-related complications and is useful for screening for debilitation in patients undergoing MHD [41]. It was standardized by Wei et al [42], and its reliability and validity were good, with a Cronbach coefficient of 0.826 and content validity of 0.98.Indicators of somatic function: due to the lack of objective indicators on the FRAIL scale, secondary evaluation indicators related to physical function were selected for measurement based on the literature review.

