### Conclusions

This study protocol presents a randomized controlled trial evaluating the efficacy of sitting Baduanjin combined with acupoint massage in improving frailty among patients undergoing MHD, addressing the gap of insufficient high-quality evidence for combined nonpharmacological interventions in this group. Its core objective is to verify whether this integrated TCM intervention alleviates frailty, enhances physical function, reduces depressive symptoms, and improves QoL, compared to routine care alone or acupoint massage alone. A key strength is the comprehensive evaluation system, integrating the FRAIL scale (primary indicator), objective physical assessments (grip strength and STS-10), and patient-reported outcomes (SDS and SF-36), alongside rigorous design (random allocation, concealed grouping, and blinded data collection and analysis), standardized protocols (8-week and thrice-weekly sessions), and detailed safety monitoring, ensuring feasibility and reliability for patients undergoing MHD. Preliminary results confirm balanced baseline characteristics across groups and good intervention safety (only mild and reversible AEs), supporting clinical applicability. If final results (anticipated Spring 2026) validate efficacy, this study will provide a scientific, low-cost nonpharmacological strategy for MHD-related frailty, enrich evidence for TCM integration into chronic kidney care, and inform clinical guidelines. Future multicenter studies with larger samples and extended follow-up are recommended to verify long-term effects and generalizability.

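### Within-arm pre-post tests at P<.05 stand beside the between-group tests as inference with no descriptive label, although they cannot answer the trial's comparative question

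*Protocol article*

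**What the plan says.** All references are to the protocol article.

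- **Statistical Inference** gives the within-arm tests: "Within-group pre-post comparisons used paired 2-tailed" t tests for normal data, otherwise rank-sum tests. The next sentence gives the between-arm tests: "Between-group differences postintervention were evaluated using one-way ANOVA (with least significant difference post hoc testing if significant) or rank-sum tests, as appropriate". Neither is ranked above the other. A separate section, Descriptive Statistical Analysis, comes just before, and the within-arm tests are not in it.
- **Statistical Analysis** sets one rule for everything: "A bilateral test was used for statistical analysis", with a 5% level.
- **Primary Evaluation Indicator** opens: "To assess the severity of frailty in patients, the scores before and after the intervention were compared as follows". It names no comparator there.
- **Conclusions** puts the objective comparatively, asking whether the combined therapy "improves QoL, compared to routine care alone or acupoint massage alone".
- The **Methods** paragraph of the Abstract also frames efficacy across arms: "scores before and after 8 weeks of treatment among the 3 groups".
- **Inclusion criteria** (Textbox 1) select on the primary outcome scale: FRAIL "with scores of ≥1 indicating prefrailty or frailty".

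**The concern.** The null hypothesis of the paired test is that the mean change in this one arm is zero. The trial's question is whether the arms differ. The paired test makes no use of the randomised comparator, so randomisation gives it no protection against causes of change that act in every arm.

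Such causes are plausible here. Patients scoring 0 on FRAIL are excluded and FRAIL is then the primary outcome, so some fall towards the population mean is expected in all three arms without any treatment effect. Repeat testing and routine dialysis care are also common to the arms. Attention is only partly shared, since the Discussion concedes that it may differ between groups.

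At stake is the reading of the primary result. A significant fall in the combined arm, or a fall that is significant there but not in control, could be reported as efficacy when the true difference between arms is zero.

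**Working it through.** The plan gives no figure for this point to reproduce. The check asks how often a within-arm test is significant when all arms improve equally and the therapy adds nothing.

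**Inputs from the Sample Size Calculation section**
- FRAIL SDs 0.96, 0.87 and 1.02. Pooled SD = √[(0.96² + 0.87² + 1.02²)/3] = √0.9063 = 0.952.
- n = 34 per arm before the 10% dropout allowance, taken here as the number evaluable (38 × 0.9 = 34.2).
- Two-sided α = 0.05.

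The stated n = 34 does not follow from the article's own formula and inputs, which give 2.52² × 0.9063 / (0.2989/2) = 38.5. That is a separate matter and does not affect this point: with 38 per arm the rates below would be slightly higher.

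**Assumed, because the article gives neither**
- Pre-post correlation r from 0 to 0.8.
- A shared improvement d, the same in every arm.

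**Formula.** SD of change = 0.952 × √[2(1 − r)]. Noncentrality = d / (SD of change / √34). The rejection rate comes from the noncentral t distribution with 33 df and critical value 2.035.

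Example, r = 0.5 and d = 0.3: SD of change = 0.952; noncentrality = 0.3/(0.952/5.831) = 1.84; rejection rate 43%.

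| Shared fall d | r = 0 | r = 0.5 | r = 0.7 | r = 0.8 |
|---|---|---|---|---|
| 0.2 | 13% | 22% | 34% | 47% |
| 0.3 | 24% | 43% | 63% | 81% |
| 0.4 | 39% | 66% | 87% | 96% |
| 0.5 | 56% | 84% | 97% | 99.7% |

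**The between-group test in the same situation.** In 20,000 simulated trials with d = 0.5, r = 0.5 and no true difference, the planned ANOVA on post-intervention values rejected in 5.1%, its nominal level. The paired test rejected in about 84% of arms in the same trials.

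**Combined significant, control not.** With equal true change and independent arms the probability is p(1 − p), which cannot exceed 25%. Over r = 0 to 0.8 it is 12–25% at d = 0.2, 16–25% at 0.3, 3–25% at 0.4 and 0.3–25% at 0.5. It falls away where both arms are almost always significant. With no shared change it is 0.05 × 0.95 = 4.8%.

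**Regression to the mean alone.** This is the one mechanism tied to a stated design feature. The model is a latent-normal 0–5 score with 20% of the source population at 0 and screened out, no change in the population, and latent correlation 0.60, 0.75 or 0.85. Mean change is −0.20, −0.14 and −0.09, and the paired test rejects in 12.8%, 12.1% and 9.5%. Other assumed score distributions give 9–14%. These rates are lower than the table's for a similar mean change because the model's score spread is wider: at latent correlation 0.60 the SD of change is near 1.4, against 0.60 to 1.35 in the table.

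**The case against.** The strongest reply is that the trial's target is already comparative. The Abstract frames efficacy across the three groups, the sample size is built on a three-group difference in means, a between-group test with post hoc contrasts is specified, and the Conclusions name the comparators. No sentence says that a within-arm P value will establish efficacy. A paired test is also a valid test of its own null, and a condensed article may leave the ranking of tests to a fuller document.

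Much of this stands. A reader might infer that the trial has no valid comparison, or that efficacy will be judged by within-arm tests; the article supports neither. The opening sentence of the primary-indicator section leads into a description of the instrument and names no test, so on its own it is weak evidence.

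A reader might also infer that any improvement shared by the arms will be declared significant. The figures above contradict that: at a shared 0.2 points, 53–87% of arms would not be significant. The larger shared changes in the table have no basis in the article and only illustrate.

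What does not stand is that this is mere silence. The article names a test, files it under inference and not under description, and applies the common 5% rule to it. That test cannot address the stated objective.

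**Conclusion.** The concern holds in a limited form. Within-arm pre-post tests have the same inferential standing as the between-group tests, and the primary indicator is worded as a before/after comparison, while the objective is comparative. A significant within-arm result does not show that the therapy adds anything.

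The size depends on assumptions. For r from 0 to 0.8, a shared fall of 0.2 points is significant in 13–47% of arms and 0.3 points in 24–81%, against 5%. Regression to the mean from the entry rule alone gives about 10–13%, and that needs the further assumption that 20% are screened out at score 0. The planned between-group ANOVA is not affected by a shared change. The point concerns how results may be interpreted and should be corrected; it does not invalidate the design.

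**What to change.** In Statistical Inference, replace the within-group significance tests with each arm's mean change and 95% CI, labelled as description only. In that section and in Primary Evaluation Indicator, add that efficacy conclusions, including those on FRAIL, rest only on the randomised between-group contrasts: combined versus control and combined versus massage.

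This takes about two sentences and needs no new data or design change. The Results section says that intervention effects will be analysed after data collection is complete, so the wording can be settled before that analysis if it has not yet been run. The small downside is that within-arm P values are no longer offered as evidence of efficacy.

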### Sample Size Calculation

The sample size calculation formula for the multigroup mean is as follows:

$$n=\varphi^{2}\left(\sum_{i}s_{i}^{2}/g\right)/\left[\sum ({\bar{X}}_{l}-\bar{X}{)}^{2}/(g-1)\right]$$

where n represents the requisite sample size for each group, g represents the number of groups, and Si is the mean (SD) for each group. The values of φ are obtained from tables α, β, ν1, and ν2, with α=.05, β=.1, ν1=2, ν2=∞, and *φ*=2.52. A 2-sided test was used in this study, which stipulates that the test level α=.05, the test efficiency 1-β=.90, and the probability of a type II error is 0.10. The FRAIL scale score was used to calculate the effect size, and the average number of patients in each group, as previously described [37], was as follows: 3.29, 2.67, and 2.58, with SD values of 0.96, 0.87, and 1.02, respectively. These data were entered into the formula to calculate n=34. Considering the shedding rate of 10%, the actual required sample size for the 3 groups was estimated to be 38 per group, totaling 114 patients.

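### The non-normal alternative for the within-group before-after comparison is named as a rank-sum test; read literally, this is an independent-samples test applied to paired scores

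*Protocol article*

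**What the plan says.** The Statistical Inference section of the protocol article uses the rank-sum label three times.

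- **Baseline comparability of the three groups:** "Continuous variables were analyzed using one-way ANOVA (normally distributed data) or rank-sum test".
- **Before-after change within a group:** the sentence opens "Within-group pre-post comparisons used paired 2-tailed" and continues "tests (normal data) or rank-sum tests. Between-group differences postintervention were evaluated using one-way ANOVA". The t test is called paired; the rank test beside it is not.
- **Post-intervention comparison of the groups:** one-way ANOVA "with least significant difference post hoc testing if significant) or rank-sum tests, as appropriate".

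The article nowhere names a signed-rank test or any other paired rank test.

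The before-after comparison is announced for the primary outcome. The section on the FRAIL scale says that "the scores before and after the intervention were compared as follows", and describes the score thus: "Each entry was assigned 1 point, and the total score ranged from 0 to 5". Textbox 1 admits only patients scoring at least 1. The tests are two-sided ("A bilateral test was used for statistical analysis"), and the Sample Size Calculation section sets "the test level α=.05, the test efficiency 1-β=.90, and the probability of a type II error is 0.10" for the three-group comparison.

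**The concern.** A rank-sum test asks whether two unrelated samples come from the same distribution. Before and after scores come from the same patients, and the question is whether patients changed. The rank counterpart of the paired t test is the signed-rank test on the differences.

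If an independent-samples test is run on paired scores, its null variance leaves out the covariance between them. With positive correlation that variance is too large, so the test rejects too seldom when nothing changed and misses part of the real change.

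The within-group result could then depend on the branch: the same data might be significant by the paired t test and not by the rank-sum test. FRAIL has at most six values and a baseline cut off at 1, so the non-normal branch is plausible for the primary score.

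**Working it through.** **1. The plan's own figures.** The article states no error rate, power or correlation for the before-after test, so there is none to reproduce. What it supplies is a two-sided α of 0.05, 34 evaluable patients per group, and 38 randomised after 10% dropout (34/0.9 = 37.8, rounded up to 38). The stated formula and inputs do not in fact return 34 per group: 2.52² × 0.906/0.149 ≈ 38.5. That is a separate matter. Both 34 and 38 were run here and lead to the same conclusion.

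**2. Assumed inputs.** The before-after correlation r is varied from 0 to 0.9 and the within-patient shift from 0.2 to 0.65 SD, because the article gives neither.

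**3. Large-sample type I error.** Under no change, pairing multiplies the variance of the rank-sum statistic by 1 − (6/π)·arcsin(r/2) for bivariate normal scores. The actual size of a nominal 5% test is therefore

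2Φ(−1.96 / √[1 − (6/π)·arcsin(r/2)]).

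At r=0.3 the factor is 1 − 0.288 = 0.712, the effective cut-off is 1.96/0.844 = 2.32, and the size is 2.0%. At r=0.5 the factor is 0.517, the cut-off is 2.72, and the size is 0.6%. At r=0.6 and 0.7 the size is 0.24% and 0.05%.

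**4. Simulation.** Scores were FRAIL-like integers from 0 to 5 (mean 3.29, SD 0.96), n=34, 4000 runs per cell. Each cell shows rejection rates in percent, rank-sum / signed-rank.

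| r | no change | 0.2 SD | 0.3 SD | 0.4 SD | 0.5 SD | 0.65 SD |
|---|---|---|---|---|---|---|
| 0 | 4.8 / 4.8 | 11 / 11 | 21 / 20 | 32 / 32 | 49 / 48 | 69 / 69 |
| 0.3 | 2.7 / 5.3 | 8 / 13 | 17 / 26 | 30 / 42 | 48 / 61 | 73 / 82 |
| 0.5 | 1.0 / 4.9 | 6 / 17 | 14 / 33 | 29 / 55 | 48 / 73 | 76 / 91 |
| 0.6 | 0.5 / 4.9 | 4 / 21 | 13 / 40 | 27 / 62 | 48 / 81 | 78 / 96 |
| 0.7 | 0.3 / 5.7 | 3 / 25 | 10 / 47 | 25 / 72 | 48 / 89 | 79 / 99 |
| 0.8 | 0.03 / 4.1 | 2 / 31 | 8 / 60 | 23 / 85 | 46 / 95 | 83 / 100 |
| 0.9 | 0.0 / 4.6 | 1 / 43 | 5 / 76 | 21 / 96 | 48 / 100 | 86 / 100 |

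Across all runs (these data and skewed lognormal data, n=34 and 38), the type I error was:

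- signed-rank: 4.0-5.7% at every r;
- rank-sum: 4.8-5.6% at r=0, 1.9-2.7% at r=0.3, 0.7-1.0% at r=0.5, 0.2-0.5% at r=0.6, 0.05-0.3% at r=0.7, and at most 0.05% from r=0.8.

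The power lost over shifts of 0.2-0.65 SD was 5-13 points at r=0.3, 9-28 at r=0.5, 9-36 at r=0.6, 9-52 at r=0.7, 5-66 at r=0.8 and 2-91 at r=0.9, with none at r=0.

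**5. Where the article's own effect scale falls.** Its only FRAIL effects are the between-group means in the sample size section. The average SD is √[(0.96² + 0.87² + 1.02²)/3] = 0.952, so the differences from the first group are 0.62/0.952 = 0.65 SD and 0.71/0.952 = 0.75 SD. These are not within-patient changes, but they are the only scale documented. At 0.65 SD the loss is at most about 20 points at any r tried. A separate bivariate normal run (n=34, r=0.3-0.8) gave about 9-16 points at 0.65 SD and 2-7 points at 0.75 SD.

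**The case against.** The strongest reply is that a label is not a procedure. Two of the three uses stand beside one-way ANOVA across three groups, where a literal two-sample rank-sum test does not fit either. The third stands beside a paired t test, so the pairing was evidently recognised. The article may use the term for rank tests in general, with the exact member of the family left to a fuller plan. This stands in part: the article does not prove which procedure will be run. It does not remove the point. Kruskal-Wallis is also a test on rank sums of independent groups, so the three-group use does not show that the label extends to paired data. One name covers two designs that need different procedures in SPSS, and as printed it is the wrong partner for the paired t test.

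Three further replies stand. Efficacy rests on comparing the three groups, and those tests are untouched. Under positive correlation the error is conservative, so it does not inflate false claims of within-group benefit. And the article names no normality check and treats FRAIL by means and SDs in its sample size, so the primary score may be analysed by the paired t test after all.

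A reader might infer that the trial will test its before-after scores with a false-positive rate near zero and a power loss of 30-70 points. The documents do not support that as fact. It presumes the literal reading, a correlation of about 0.6-0.7 or more, and small to moderate shifts, none of which the article establishes.

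**Conclusion.** The stated method for non-normal before-after data is wrong as written, or at best ambiguous, and should be corrected. How much it matters depends on two quantities that the article does not give. If the literal test is run and r lies between 0.3 and 0.9, the type I error is about 0-3% instead of 5%. The loss of power ranges from a few points to more than 30, and the larger losses need r of about 0.6 or above with shifts of roughly 0.2-0.5 SD. With uncorrelated scores nothing is lost. The defect is confined to the within-group results and does not touch the randomised comparison.

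**What to change.** In the within-group sentence of Statistical Inference, replace the rank-sum wording with: Wilcoxon signed-rank test on the paired differences. In the two sentences on the three groups, name the Kruskal-Wallis test. If the label was meant loosely, this only makes the intended paired procedure explicit.

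The cost is a few words of text. SPSS already offers both tests, and no new data are needed. The article's Results section places the full analysis of intervention effects after data collection is complete, so on its own account the wording can be settled before that analysis.

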### Evaluation Indicators

#### Overview

Data collection will be conducted in strict accordance with the established schedule to ensure the integrity and timeliness of information. Research team members must be trained in standardized measurement methods to minimize measurement bias. Furthermore, baseline data (including demographic characteristics, FRAIL scale scores, grip strength, 10 times sit-to-stand (STS-10) results, Self-Rating Depression Scale (SDS) scores, and QoL (Short Form Health Survey Questionnaire [SF-36]) scores must be collected before the intervention, and follow-up data for the same indicators must be collected after 8 weeks of treatment. The specific research program, including the timing of enrollment, intervention implementation, and indicator assessment, is detailed in Table 2.

**Table 2. T2:** Enrollment schedule, interventions, and evaluation.

Research period	Registration phase (1 week)	Divide into groups (>1 week)	Intervene (8 weeks)
Point in time			
Join a group	✓		
Eligibility screening	**✓**		
Informed consent	**✓**		
Divide into groups		**✓**	
Intervene			
Control group			✓
Routine treatment and nursing			**✓**
Routine treatment and nursing+acupressure group			**✓**
Conventional treatment and nursing+sitting Baduanjin combined acupressure			**✓**
Assessment			
FRAIL^a^ Scale score			**✓**
Grip strength			**✓**
STS-10^b^			**✓**
SDS^c^			**✓**
SF-36^d^			**✓**

a FRAIL: Fatigue, Resistance, Ambulation, Illness, and Weight Loss.

b STS-10: 10 times sit-to-stand.

c SDS: Self-Rating Depression Scale.

d SF-36: Short Form Health Survey Questionnaire.

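### The between-group comparison of FRAIL leaves out the baseline score that is collected and does not fix one primary test; it is valid under randomisation but inefficient, and can be improved at no data cost

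*Protocol article*

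**What the plan says.** The protocol's Statistical Inference section sets out the comparison between arms: "Between-group differences postintervention were evaluated using one-way ANOVA (with least significant difference post hoc testing if significant) or rank-sum tests, as appropriate". That sentence gives no criterion for the choice. The sentences before it, on baseline variables and on pre-post changes, use normality of the data, as does the Descriptive Statistical Analysis section.

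Baseline values have two uses in the section: a check that the arms are comparable, and tests within each arm ("Within-group pre-post comparisons used paired 2-tailed" *t* tests, or rank-sum tests). Neither brings baseline into the comparison between arms.

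Baseline is nevertheless collected in full. The Overview under Evaluation Indicators lists FRAIL, grip strength, STS-10, SDS and SF-36 as data that "must be collected before the intervention, and follow-up data for the same indicators must be collected after 8 weeks of treatment".

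The primary indicator is an integer score: "Each entry was assigned 1 point, and the total score ranged from 0 to 5". The Sample Size Calculation section plans on group means of this score, with "the test level α=.05, the test efficiency 1-β=.90" and a formula for comparing several means. It includes no covariate and no rank test.

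**The concern.** Two features of the between-group sentence deserve attention.

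First, the comparison uses week-8 values alone. A patient's FRAIL score at week 8 is likely to be related to the score at entry. Leaving baseline out puts that explainable variation into the error term. Chance differences between arms at baseline then add noise to the estimated effect, and power that could be had for nothing is lost.

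Second, the primary test is not one test. If normality decides, a 0 to 5 integer score may well be sent to a rank test, although the trial was sized on a comparison of means. A rank test gives a P value but no difference in FRAIL points. If the choice is instead a matter of judgement, it could be made after the data are seen.

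At stake are the precision of the primary result and the advance definition of what it estimates.

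**Working it through.** **Inputs** (Sample Size Calculation): "The FRAIL scale score was used to calculate the effect size"; group means and SDs "3.29, 2.67, and 2.58, with SD values of 0.96, 0.87, and 1.02, respectively"; two-sided α = 0.05; "ν1=2, ν2=∞, and *φ*=2.52"; stated n = 34 per arm, raised to 38 for 10% dropout.

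**Step 1. The plan's own figure.**
- Mean variance: (0.96² + 0.87² + 1.02²)/3 = (0.9216 + 0.7569 + 1.0404)/3 = 0.9063.
- Grand mean: (3.29 + 2.67 + 2.58)/3 = 2.8467.
- Between-group sum of squares: 0.1965 + 0.0312 + 0.0711 = 0.2989.
- n = φ² × mean variance / (sum of squares / 2) = 2.52² × 0.9063 / 0.1494 = 38.5.

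The formula therefore gives 39 per arm, and the stated 34 is not reproduced. That is a separate sample-size finding. It matters here only because it explains why the starting power below is under 90%.

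**Step 2. Power of the unadjusted ANOVA.** The noncentrality is λ = n × 0.2989 / 0.9063. At n = 34, λ = 11.21 with 2 and 99 degrees of freedom, and power is 84.8%. At n = 38 it is 88.8%.

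**Step 3. Power with baseline FRAIL as covariate.** If r is the correlation between baseline and week-8 FRAIL within arms, the residual variance becomes 0.9063 × (1 − r²), and one error degree of freedom is spent. The protocol gives no r, so a range is shown, for 34 evaluable per arm.

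| r (assumed) | Residual variance | λ | Power |
|---|---|---|---|
| unadjusted | 0.906 | 11.21 | 84.8% |
| 0.1 | 0.897 | 11.33 | 85.2% |
| 0.2 | 0.870 | 11.68 | 86.3% |
| 0.3 | 0.825 | 12.32 | 88.2% |
| 0.4 | 0.761 | 13.35 | 90.7% |
| 0.5 | 0.680 | 14.95 | 93.6% |
| 0.7 | 0.462 | 21.98 | 99.0% |

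The gain is 0.4 points at r = 0.1 and about 14 points at r = 0.7. At no value in the range does adjustment lose power.

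**Step 4. Cost of switching to a rank test.** Normal scores with the planning means and SDs were rounded and clipped to integers 0 to 5, with 10,000 simulated trials of 34 per arm. ANOVA had 80.1% power and Kruskal-Wallis 78.5%, a difference of 1.6 points. A repeat simulation gave 79.8% and 77.9%, a difference of 1.9 points. With no true difference, the rejection rates were 5.2% and 5.3%. Power is below the 84.8% of Step 2 for both tests because rounding adds variance.

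**Step 5. Where a normality rule would lead.** In the same simulation, Shapiro-Wilk never accepted normality in all three arms together, so a rule based on it always chose the rank test. Shapiro-Wilk is an assumption, because the protocol names no normality test.

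**The case against.** The strongest reply is that nothing here is invalid. With sound randomisation, a post-only comparison is unbiased and keeps its type I error, and Kruskal-Wallis is a legitimate test for a 0 to 5 score. The benefit of adjustment rests wholly on a correlation the protocol does not give, and at r of 0.1 or 0.2 it is at most 1.5 points. The name of the normality test and the post hoc procedure after a rank test are details that an analysis plan may supply. All of this stands, and it limits the point to efficiency and pre-specification. It does not remove the point, because the between-group method is something the protocol states, not something it leaves out.

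Three stronger readings are tempting, and the protocol does not support them.

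- A reader might infer that the rank test seriously weakens the trial. Step 4 shows a loss of about 1.5 to 2 points and no excess of false positives.
- A reader might infer that significant change within an arm will be taken as efficacy. The Statistical Inference section has a separate between-group comparison, and the Abstract and Conclusions frame efficacy as a comparison among the groups.
- A reader might infer from Table 2, where assessments are ticked only in the 8-week column, that baseline is not measured. The table may have been damaged in text extraction. The Overview and Data Collection sections both require measurement before treatment, and FRAIL is itself an inclusion criterion.

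Adjustment should also not be presented as the remedy for the stated n of 34. That shortfall needs its own correction.

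**Conclusion.** The point holds as an improvement in efficiency and pre-specification, not as a flaw that invalidates the comparison. The protocol fixes a post-only comparison although baseline is available, and it leaves the primary test to the data.

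With the planning values and 34 evaluable patients per arm, omitting baseline costs between 0.4 and about 14 points of power for correlations from 0.1 to 0.7. For correlations from 0.3 to 0.5 the cost is 3 to 9 points. These figures assume a linear relation with a common slope, equal variances and an undocumented r. The unfixed test costs little power. Its harm is that the primary test and effect measure are not settled before the data are seen, and that the rank route gives no effect in FRAIL points. That normality governs the choice between arms is read from the neighbouring sentences.

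**What to change.** Before outcomes are analysed, replace the between-group sentence with one primary analysis: ANCOVA of week-8 FRAIL on arm with baseline FRAIL as covariate, applied whatever a normality check shows. Report adjusted pairwise differences in FRAIL points with 95% confidence intervals. Keep a rank-based or ordinal analysis as a sensitivity analysis. Use the same baseline-adjusted model for grip strength, STS-10, SDS and SF-36. State that conclusions on efficacy rest on comparisons between arms and that changes within arms are descriptive.

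The cost is wording only. No further data or visits are needed, and the SPSS version named in the protocol fits ANCOVA. The Results section says that the analysis of intervention effects awaits the end of data collection, so, going by the article, the change can still be made in advance.
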